### Statistical analysis

All recorded variables will be tabulated using summary statistics for continuous variables and frequency tables (absolute and relative) for categorical variables. All outcomes will be stratified by country.

Logistic regression analysis will be used to analyse binary variables (e.g. the association between the asthma control level and quality of life in the cross-sectional phase). Models will include confounding factors if identified by the exploratory analysis. As measures of association between the response variable (e.g. the asthma control level) and the independent variables, the odds ratios (ORs) with the relative 95% CI along with the p-value will be reported. For continuous variables, the estimated OR will be expressed for a change of *c* units in the covariate.

The analyses of the results of the longitudinal phase will be conducted using mixed-effect models (SAS Proc MIXED) to estimate the means of the changes in the scores over time from the cross-sectional phase visit.

The healthcare costs will be evaluated by descriptive analysis, considering the time frames of 3 months before the cross-sectional phase visit and the longitudinal phase period.

The number of severe exacerbations in the last 12 months before the cross-sectional phase visit and the number of severe exacerbations per patient/year at each visit will be descriptively analysed overall and by level of asthma control. The rate of severe exacerbations per patient/year will be calculated as the total number of experienced severe exacerbations over the longitudinal phase on total number of days of observation of patients at risk. The time to first asthma severe exacerbation during the longitudinal phase will be analysed with the Kaplan-Meier survival analysis, and their significance by the log-rank test. Predictors of exacerbations will be analysed by means of a multivariate logistic model. A stepwise selection approach will be used to identify the most significant prognostic factors and to eliminate the unimportant ones. Using this methodology, a final predictive model containing just the important variables will be created.

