## Objectives

Table 1 summarises the primary and secondary objectives of the study. The primary objectives of the cross-sectional phase are to evaluate the proportions of patients with controlled, partly controlled and uncontrolled asthma, and to assess the health-related quality of life and the factors associated with asthma control in a real-life population of asthmatic patients.

**Table 1 T1:** Primary and secondary objectives to be investigated

	**Cross-sectional phase**	**Longitudinal phase**
**Primary objectives**	• Prevalence of patients with controlled or uncontrolled/partly controlled asthma	• Proportions of patients with controlled, partly controlled and uncontrolled asthma after 12 months from the cross-sectional phase visit
	• Health-related quality of life	• Proportion of patients with uncontrolled/partly controlled asthma switching to controlled asthma after 12 months from the cross-sectional phase visit
	• Factors associated with asthma control	• Changes in quality of life after 12 months
		• Factors associated with the gain of asthma control
**Secondary objectives**	• Proportion of asthmatic smokers and their level of asthma control	• Association between (current) level of asthma control and (future) risk of exacerbations
	• Antiasthmatic therapies	• Relation between change in asthma control and change in rate of exacerbations during the longitudinal phase (including stratified analyses according to GINA treatment level)
	• Medication adherence	• Antiasthmatic therapies
	• Healthcare costs over 3 months before the cross-sectional phase visit	• Proportion of patients with uncontrolled/partly controlled asthma that reach control after 3 and 6 months from cross-sectional phase visit
	• Rate of severe exacerbations in the last 12 months before the cross-sectional phase visit	• Medication adherence
	• Reasons for poor control according to the Investigators’ and the patients’ opinion	• Healthcare costs
	• Lung function parameters, if available	• Rate of severe exacerbations and the time to first severe exacerbation
		• Reasons for poor control according to the Investigators’ and the patients’ opinion
		• Lung function parameters, if available

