## Methods/design

### Study design

Figure 1 shows the design of the cross-sectional phase and the prospective phase of the study. Subjects satisfying entry criteria will be evaluated in the cross-sectional phase of the study. Asthmatic patients with uncontrolled/partly controlled asthma will be followed for the 12-month prospective phase. Follow-up visits will take place approximately 3, 6 and 12 months after the cross-sectional phase visit.

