### Sample size

Based on available data from the literature, the proportion of patients with controlled asthma at initial visit (defined as an ACQ score ≤ 0.75) is expected to be about 37.5% [15]. Considering that patients with uncontrolled and partly controlled asthma at the cross-sectional phase visit will be included in the prospective phase, the percentage of patients with controlled asthma at month 12 is expected to be approximately 45% [27].

By enrolling 8,150 patients, it is expected that 5,094 patients should have uncontrolled/partly controlled asthma at the cross-sectional phase visit. The proportion of patients expected to drop out, for any reason, during the 12-month longitudinal phase is 20%. Therefore, 4,075 patients should be evaluable at month 12, which allows estimating the expected 45% of patients reaching asthma control at the end of longitudinal phase with a precision of ± 1.5% (two-sided 95% CI).

With regard to the assessment of quality of life, a standard deviation (SD) for the Mini AQLQ overall score of approximately 1.21 units can be estimated from the literature [28]. If 4,075 patients are evaluable for the analysis of the Mini AQLQ overall score from the cross-sectional phase visit, then the distance from the boundaries of the two-sided 95% CI to the point estimate will be 0.037 units. Therefore, considering the expected patients reaching asthma control at the end of the longitudinal phase, the distance from the boundaries of the two-sided 95% CI to the point estimate will be 0.055 units.

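### The severe exacerbation rate is labelled per patient-year, but its stated formula divides by days with no conversion and so gives a per-day rate (minor, wrong as written)

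*Protocol article*

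**What the plan says.** In the protocol article, the Statistical analysis section gives the quantity its name and unit with "The rate of severe exacerbations per patient/year will be calculated as". The numerator and the denominator follow at once: "the total number of experienced severe exacerbations over the longitudinal phase on total number of days of observation of patients at risk". No multiplier is attached and no other formula for the rate is given.

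The sentence before it uses the same unit for a by-visit summary: "the number of severe exacerbations per patient/year at each visit will be descriptively analysed overall and by level of asthma control". That sentence also covers the number of severe exacerbations in the 12 months before the first visit.

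Table 1 in the Objectives section lists the exacerbation rate as a secondary objective in both phases. For the cross-sectional phase the entry is "Rate of severe exacerbations in the last 12 months before the cross-sectional phase visit". For the longitudinal phase, the rate is listed together with the time to first severe exacerbation.

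**The concern.** The unit in the name and the unit that the formula yields do not agree. A count of events divided by a number of days has the unit events per patient-day. To be a rate per patient-year it needs the exposure in years, or a factor of 365.25.

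At stake is the absolute value of a listed secondary outcome of the longitudinal phase. If the sentence were programmed as it stands, the table would carry a per-day figure under a per-year heading. It would sit beside a 12-month history that is already on a yearly basis, so the two could not be read together. The by-visit figures are affected as well. Visits fall at about 3, 6 and 12 months, so a yearly figure for a shorter interval cannot be had without annualising, and the only formula in the article leaves that step out.

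**Working it through.** **Is there a figure to reproduce?** No. The article gives no expected or observed exacerbation rate, so the check is one of units.

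**Inputs from the article**
- Named unit: per patient-year (Statistical analysis).
- Numerator E: total severe exacerbations in the longitudinal phase (Statistical analysis).
- Denominator D: total patient-days at risk, unscaled (Statistical analysis).
- Length of follow-up (Study design): "Asthmatic patients with uncontrolled/partly controlled asthma will be followed for the 12-month prospective phase".
- Patients entering follow-up (Sample size): "By enrolling 8,150 patients, it is expected that 5,094 patients should have uncontrolled/partly controlled asthma at the cross-sectional phase visit". With 20% dropout, 4,075 are evaluable at month 12.

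The two patient numbers reproduce: 8,150 × (1 − 0.375) = 5,093.75, stated as 5,094; and 5,093.75 × 0.80 = 4,075, as stated. They serve below only to give a realistic amount of exposure.

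**Step 1: the two formulas**
- As written: E / D.
- As named: E / (D / 365.25) = 365.25 × E / D.
- Ratio of named to written: 365.25. Both E and D cancel, so the ratio does not depend on event count, follow-up or dropout. With a 365-day year it is 365, a difference of 0.25 / 365.25 = 0.07%.

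**Step 2: illustration.** The true rates are assumptions, since the article gives none. Exposure is 4,075 patients × 365.25 days = 1,488,394 patient-days.

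| Assumed true rate per patient-year | Events | Formula as written | With / 365.25 |
|---|---|---|---|
| 0.1 | 408 | 0.000274 | 0.100 |
| 0.3 | 1,222 | 0.000821 | 0.300 |
| 0.5 | 2,038 | 0.00137 | 0.500 |
| 1.0 | 4,075 | 0.00274 | 1.000 |

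**Step 3: does dropout change it?** Let the 5,094 − 4,075 = 1,019 dropouts each add half a year (an assumption). Exposure becomes (4,075 + 509.5) × 365.25 = 1,674,489 patient-days. At 0.3 per patient-year there are about 1,375 events, and 1,375 / 1,674,489 = 0.000821 again. The ratio stays at 365.25.

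**Step 4: scale against the prior-year count.** A patient's count over 12 months is already events per patient-year. If the underlying rate were 0.3 in both periods, the two entries would read 0.3 and 0.000821, and the gap would be purely one of units.

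**Step 5: what is not affected.** A constant multiplier cancels from any ratio of rates between control levels or countries. The Kaplan-Meier and log-rank analysis, the logistic model for predictors of exacerbation and the sample size do not use this rate. None of the primary objectives in Table 1 uses it either.

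**The case against.** The strongest reply is that nobody would be misled. The article names the yearly unit twice; days are simply how exposure is accumulated; and turning days into years is routine programming. An analyst asked for a rate per patient-year would be unlikely to report 0.000821 under that heading. The article is also a condensed text, and a fuller plan may exist.

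Much of this stands, and it sets the weight of the point: the likely cause is a wording omission and the likely outcome is that it is noticed. It does not remove the point. The article did not leave the calculation to another document. It chose to state a formula, and that formula contradicts its own label.

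Two stronger readings are tempting, but the article does not support them.

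- A reader might infer that the slip would produce a false fall in a planned comparison of the prior year with follow-up, through the Table 1 objective on change in exacerbation rate. Table 1 places that change within the longitudinal phase. Read that way, both sides carry the same constant and the relative change is unaffected. The article plans no test of prior year against follow-up; it only describes the two quantities.
- A reader might also infer that a pooled rate implies Poisson intervals that are too narrow because exacerbations cluster within patients. The article states no Poisson model, standard error or confidence interval for this rate, and its treatment of these quantities is descriptive. There is no interval to criticise, and nothing in a unit slip calls for a negative binomial model.

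**Conclusion.** The point holds as a minor error of wording that is wrong as written. The stated rule returns a per-day rate, 365.25 times smaller than the per patient-year rate it claims to define. The factor is exact for a 365.25-day year and needs no assumption about events or follow-up; only the illustrative rates in the table are assumed. The consequence is confined to the absolute value of a secondary, descriptive outcome, to the by-visit figures in the same unit, and to their reading beside the prior-12-month count. Conclusions that rest on relative comparisons, on the time-to-event or logistic analyses, on the sample size or on the primary objectives are unaffected.

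**What to change.** In the Statistical analysis section, define the rate as the total number of severe exacerbations in the longitudinal phase divided by (total days of observation of patients at risk / 365.25). State that the per patient-year figures at each visit use the same formula, with the events and days of the period they cover. The prior-12-month count needs no conversion, since it is already on a yearly basis.

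The cost is one phrase in one sentence. No data, design, sample size or other analysis changes.

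### The logistic model for exacerbation predictors takes no account of observation time, so with 20% drop-out planned its odds ratios can be biased if drop-out differs by covariate

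*Protocol article*

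**What the plan says.** The Statistical analysis section of the protocol article fixes the model class: "Predictors of exacerbations will be analysed by means of a multivariate logistic model". It then adds variable selection: "A stepwise selection approach will be used to identify the most significant prognostic factors and to eliminate the unimportant ones". It mentions no person-time, censoring or offset for this model.

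The same paragraph treats the other exacerbation analyses differently. The rate is calculated as "the total number of experienced severe exacerbations over the longitudinal phase on total number of days of observation of patients at risk", and time to first severe exacerbation is analysed by Kaplan-Meier with a log-rank test.

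The Sample size section gives the expected loss: "The proportion of patients expected to drop out, for any reason, during the 12-month longitudinal phase is 20" per cent. It also states "By enrolling 8,150 patients, it is expected that 5,094 patients should have uncontrolled/partly controlled asthma at the cross-sectional phase visit" and "Therefore, 4,075 patients should be evaluable at month 12".

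The text of the Objectives section counts predictors of future exacerbation risk among the primary objectives of the prospective phase. Table 1 lists the association between control and exacerbation risk as secondary.

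**The concern.** A logistic model for any exacerbation, yes or no, estimates a risk over one window common to all patients. About one patient in five is expected not to have the full 12 months. Such patients must be counted as event-free for time that nobody observed, kept only if they had an event, or left out. The first two choices tie the outcome to the length of follow-up. A covariate that predicts leaving the study can then look like a predictor of exacerbation, or a real predictor can be weakened or exaggerated. Selection by significance may carry such a signal into the final predictive model.

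Factors such as smoking, non-adherence or country could plausibly be related to drop-out in a 12-country observational cohort, though the article gives no data on this.

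**Working it through.** **The plan's own figures**

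- Entering the longitudinal phase: 8,150 × (1 − 0.375) = 5,093.75, stated as 5,094.
- Evaluable at month 12: 5,093.75 × 0.80 = 4,075, as stated.
- Without full follow-up: 5,094 − 4,075 = 1,019.

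These figures reproduce.

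**Assumptions, because the article gives no exacerbation risk and no drop-out by covariate**

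- Two groups of equal size, with average drop-out of 20%.
- Exponential time to first severe exacerbation with rate λ; 12-month risk in the reference group 10-40%.
- Drop-out exponential with rate μ and independent of exacerbation within each group.

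**Formulas**

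- Observed event: p = λ/(λ+μ) × (1 − exp(−(λ+μ))).
- Completed without event: c = exp(−(λ+μ)).
- Odds if drop-outs are coded event-free: p/(1 − p).
- Odds if only completers and patients with events are kept: p/c.

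**Worked case: no true effect, 20% risk, drop-out 10% versus 30%**

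- λ = −ln 0.8 = 0.223; μ = −ln 0.9 = 0.105 and −ln 0.7 = 0.357.
- Low drop-out: p = 0.223/0.3285 × 0.28 = 0.190; c = 0.72.
- High drop-out: p = 0.223/0.580 × 0.44 = 0.169; c = 0.56.
- Coded event-free: OR = (0.1693/0.8307)/(0.1902/0.8098) = 0.868.
- Completers plus events: OR = (0.1693/0.56)/(0.1902/0.72) = 1.145.

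**OR for a factor with no effect (higher versus lower drop-out group), 12-month risk 10-40%**

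| Drop-out | Coded event-free | Completers plus events |
|---|---|---|
| 20% v 20% | 1.00 | 1.00 |
| 25% v 15% | 0.92-0.94 | about 1.07 |
| 30% v 10% | 0.84-0.88 | 1.14-1.15 |
| 35% v 5% | 0.77-0.82 | 1.22-1.24 |

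**A real effect.** A hazard ratio of 2 at 20% reference risk has an OR of 2.25 under full follow-up. With 30% drop-out in the higher-risk group and 10% in the other, it becomes 1.88 or 2.59 under the two codings. With equal drop-out, real effects (hazard ratio up to 2) change by at most about 7%.

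**Does the drop-out pattern matter?** Take drop-out uniform over the year and 0.5 events per year.

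- Risk over a full year: 1 − exp(−0.5) = 0.393. Risk observed in a drop-out: 1 − 0.393/0.5 = 0.213.
- 30% drop-out: 0.7 × 0.393 + 0.3 × 0.213 = 0.339. 10% drop-out: 0.9 × 0.393 + 0.1 × 0.213 = 0.375.
- OR 0.855. With 2,547 per group the standard error of the log OR is 0.0585, so z = −2.69.

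This agrees with the table.

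**Twelve-month completers only.** Under independent drop-out, the risk among completers is 1 − exp(−λ) in both groups, so the OR stays at 1.00. The cost is information. In the uniform example, drop-outs hold 0.2 × 0.213 = 0.043 of 0.8 × 0.393 + 0.043 = 0.357, about 12% of first events. With 1,783 and 2,292 completers (70% and 90% of 2,547) the standard error is 0.0646, about 10% wider than 0.0585.

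**The case against.** A reader might infer that the planned odds ratios will be biased, or that any factor linked to drop-out will look falsely protective. The article does not support that.

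- It does not say how early leavers enter the model, and a condensed article may leave that to the full protocol or analysis plan. The direction of bias reverses between two plausible codings, and a completers-only model is unbiased under the same independence condition that a Cox model needs.
- The size depends on the scenario. Under event-free coding and uniform drop-out, 25% versus 15% with 0.3 to 0.8 events per year gives z of only −1.0 to −1.7. With 30% versus 10% at 0.2 per year, z is −1.7. A conventionally significant false signal needs strongly differential drop-out and a fairly high event rate.
- A 12-month yes/no outcome is a legitimate prediction target, and the exacerbation analyses as a whole do not neglect follow-up time.

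All of this stands, and it makes the bias conditional. It does not rescue the model choice: each coding is either open to bias when drop-out is differential, or discards observed data.

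Other arguments that might be attached to the point should be left out. Treating one and several exacerbations alike is a choice of estimand, shared by Kaplan-Meier and Cox analyses of first events. The article does say "Follow-up visits will take place approximately 3, 6 and 12 months after the cross-sectional phase visit", but nothing links visit timing to any covariate. A disagreement with the rate and survival results cannot be presumed, since odds ratios differ from rate ratios even with complete follow-up. Centre effects have no bearing on observation time.

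**Conclusion.** The point holds in conditional form. The article fixes a model class that ignores observation time for an aim that its Objectives text calls primary, while expecting about 1,019 of 5,094 patients to lack full follow-up and using follow-up time in the neighbouring analyses. For a factor with no effect, the distortion is roughly 6-8% downwards or 7% upwards at 25% versus 15% drop-out, and 12-16% downwards or 14-15% upwards at 30% versus 10%, depending on coding. These sizes rest on assumed risks of 10-40%, assumed drop-out patterns and independence of drop-out and exacerbation within groups. With equal drop-out a null factor is unaffected. The change is worth making, but the documents do not show that the results would be wrong without it.

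**What to change.** Replace the logistic model for predictors of severe exacerbations with one of the following, fitted to all longitudinal-phase patients:

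- a multivariable Cox model for time to first severe exacerbation, which matches the planned Kaplan-Meier analysis; or
- a negative binomial model for the number of severe exacerbations with log(days observed) as offset, which matches the planned rate and also uses repeat events.

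If drop-out is independent of exacerbation given the covariates, these target the hazard or rate ratio whatever the drop-out pattern.

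The cost is a change of wording. Event times and days at risk are already needed for the Kaplan-Meier and rate analyses. Results would be reported as hazard or rate ratios instead of odds ratios. Neither model cures drop-out that depends on unmeasured exacerbation risk.

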### Study population

The study population will include approximately 8,150 patients attending about 160 outpatient hospitals or General Practice clinics distributed across 12 European countries (Austria, Belgium, France, Germany, Greece, Hungary, Italy, the Netherlands, Poland, Spain, Turkey and the United Kingdom). At least 400 patients in about eight centres will be enrolled in each participating country. Consecutive patients visiting the centre during the estimated 12-month recruitment period will be enrolled.

Male and female adult (aged ≥18 years) patients with a clinical diagnosis of asthma (according to GINA guidelines and confirmed by a chest physician) for at least 6 months, and receiving the same antiasthmatic drugs in the last 4 weeks before enrolment, will be eligible for study participation after signing the informed consent.

Patients participating in a clinical trial within the previous 4 weeks or patients suffering from conditions and illnesses that might interfere with the study purpose, according to the investigator’s evaluation, will be excluded from the study.

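### Stepwise selection of exacerbation predictors, and confounders chosen from the same data, can exaggerate weak associations; both sets should be fixed in advance

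*Protocol article*

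**What the plan says.** The Statistical analysis section of the protocol article contains two separate rules.

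- **Logistic models of binary outcomes** (the example given is asthma control level against quality of life): "Models will include confounding factors if identified by the exploratory analysis". The same paragraph says that odds ratios with 95% confidence intervals and p-values will be reported.
- **Predictors of severe exacerbations**, analysed with a multivariable logistic model: "A stepwise selection approach will be used to identify the most significant prognostic factors and to eliminate the unimportant ones". The stated product is that "a final predictive model containing just the important variables will be created".

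Both rules serve declared aims. Table 1 lists factors associated with asthma control, and with gaining control, as primary. The Objectives text also names predictors of future exacerbations among the primary aims of the prospective phase, whereas Table 1 places exacerbation risk among the secondary objectives.

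**The concern.** These are stated methods, so the concern does not rest on missing detail. A variable enters the exacerbation model because its estimate in this sample happened to be large relative to its standard error. When the same sample then supplies the odds ratio, interval and p-value as though the model had been fixed beforehand, three things can follow:

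- Weak true predictors are retained mainly in samples that overestimate them, so their reported odds ratios lie too far from 1.
- Every null variable retained at the 5% level has a 95% interval that excludes 1, which is its true value. It appears in the final table among the variables called important, while the discarded candidates are no longer visible.
- Under the confounder rule, the adjustment set for the asthma-control models depends on the sample. A variable known on clinical grounds to confound may be left out.

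At stake is how far a reader can rely on the published list of exacerbation predictors and on the adjusted odds ratios for asthma control.

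**Working it through.** **The plan's own figures.** All inputs are from the Sample size section.

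- Not controlled at first visit: 8,150 × (1 − 0.375) = 5,093.75, stated as 5,094.
- Evaluable at month 12 after 20% dropout: 8,150 × 0.625 × 0.80 = 4,075, as stated.
- Precision for 45%: 1.96 × √(0.45 × 0.55 / 4,075) = 0.0153, stated as ±1.5%.

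These reproduce. The article gives no figure for the stepwise model, so its behaviour was examined by simulation.

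**Assumptions, none of them from the document.** n = 4,075 is taken as the number available to the exacerbation model. There are 25 standardised candidates with pairwise correlation 0.2: 15 null, 4 with true OR 1.1, 3 with 1.2 and 3 with 1.5. Risk of an exacerbation is 5% to 30%. Backward elimination at p < 0.05 stands in for the unspecified stepwise rule. There were 150 runs per setting.

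**Results for retained variables at n = 4,075.** Mean OR is the exponential of the mean log-OR.

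| Event risk (events) | True OR 1.10: mean OR; coverage | True OR 1.20: mean OR; coverage | True OR 1.50: mean OR; coverage |
|---|---|---|---|
| 5% (204) | 1.23; 0.86 | 1.27; 0.94 | 1.53; 0.93 |
| 10% (408) | 1.18; 0.90 | 1.23; 0.96 | 1.52; 0.94 |
| 20% (815) | 1.14; 0.95 | 1.22; 0.95 | 1.51; 0.96 |
| 30% (1,222) | 1.13; 0.95 | 1.21; 0.95 | 1.51; 0.94 |

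- **Inflation.** For a true OR of 1.10 at 5% risk, the log-OR ratio is ln 1.231 / ln 1.10 = 0.208 / 0.0953 = 2.18. At 30% risk it is ln 1.133 / ln 1.10 = 0.125 / 0.0953 = 1.31. For a true OR of 1.50 the inflation is 1% to 5%.
- **Coverage.** The full model without selection gave 0.94 to 0.96 for all effects. At OR 1.10 and 5% risk, about 0.27 × 4 × 150 = 162 retained estimates underlie the 0.86. The Monte Carlo standard error is therefore roughly √(0.859 × 0.141 / 162) = 0.027, and the shortfall from 0.95 exceeds chance. At 20% and 30% risk no loss is seen.
- **Null variables.** Coverage among retained nulls was 0, as it must be when retention requires p < 0.05. At least one null was retained in 53% to 62% of runs; theory for 15 independent nulls gives 1 − 0.95^15 = 0.54.
- **Discrimination.** Optimism in the AUC of the pooled model was about 0.01 or less.

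**One country at the minimum size.** The Study population section says: "At least 400 patients in about eight centres will be enrolled in each participating country". That gives 400 × 0.625 × 0.80 = 200 evaluable patients and, at an assumed 20% risk, 40 events. In 200 runs, true ORs of 1.2 and 1.5 became 1.8 and 2.0 when retained, coverage among retained non-null variables was 0.37 to 0.83, and AUC optimism was 0.09. At this size the full model with 25 candidates also fell short, with coverage of 0.91 to 0.93.

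**The case against.** The strongest reply is that the study is large. With about 4,075 patients, moderate and strong predictors are hardly affected, and a pooled model used purely for prediction shows little optimism. The study is observational, Table 1 ranks exacerbation risk as secondary, and no sample-size or precision statement depends on the stepwise model. All of this stands, and it limits the size of the point.

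Several stronger readings are tempting, but the document does not support them:

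- **Stepwise selection as the source of the false positives.** A reader might take the 53% to 62% of runs with a retained null as harm caused by selection. It is ordinary 5% multiplicity, and a full model has just as many nulls with p < 0.05. The difference lies in the reporting: the full model shows every candidate and keeps nominal coverage over all of them, whereas the selected model shows only the survivors.
- **An unvalidated model.** The article is silent on validation, candidate list and entry level. A condensed article commonly leaves these to the full protocol or analysis plan, so the silence is no finding.
- **Adjustment by significance.** The article gives no criterion for the exploratory analysis. What it does say is that confounder choice depends on the data.
- **Stepwise selection in the primary asthma-control models.** The stepwise sentence belongs to the exacerbation analysis, and the confounder sentence stands in another paragraph.
- **Country-level stepwise models.** Outcomes are to be stratified by country, but the article does not say that this selection will be repeated within countries. The figures at n = 200 apply only if it is.

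**Conclusion.** The point holds in a limited form. Choosing exacerbation predictors by stepwise significance, and confounders for binary-outcome models by data exploration, is a poor stated choice for estimating associations.

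Material exaggeration is confined to weak predictors (true OR about 1.1) and to settings with few events. Loss of coverage for such predictors appears at 5% to 10% risk. Retained null variables always carry a misleading interval. For true ORs of 1.2 or more with at least about 10% of patients having an exacerbation, the pooled analysis is little affected.

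These sizes depend on the assumed number of candidates, their effects and correlation, the event risk and the 5% retention level. The direction of the bias does not. The effect of the confounder rule was not quantified, because its criterion is not given. This is a worthwhile, inexpensive improvement and does not threaten the study's main estimates of prevalence or precision.

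**What to change.** - **Exacerbation model.** Replace the stepwise sentence with a full logistic model whose candidates are fixed in advance on clinical grounds from variables already collected. Examples are age, sex, smoking, occupational exposure, comorbidities, treatment level, MMAS-4, prior-year severe exacerbations, baseline ACQ and country. Keep all terms whatever their p-value, and base odds ratios and intervals on this model.
- **Asthma-control models.** Replace the confounder sentence with a set fixed in advance. Baseline ACQ belongs only in the longitudinal models, because the ACQ defines the outcome in the cross-sectional ones.
- **If a reduced predictive model is still wanted.** Derive it by penalisation with bootstrap correction for optimism, label it as prediction only, and report no naive confidence intervals or p-values from it. Penalisation alone does not restore valid intervals.

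The cost is a change of analysis wording, modest programming, a longer model table and slightly wider intervals. No further patients or data items are needed.
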